## Abstract

**Background:**

The burden of sick leave for society and organisations underlines the urgent need to prevent sick leave. An effective workplace intervention for organisations to shorten sick leave episodes is the Participatory Approach (PA). In this study, we hypothesize that implementation of the PA for supervisors within organisations may prevent sick leave as well. However, implementation of the PA within an organisation is difficult, and barriers at different levels (employee, supervisor and organisational) exist. Therefore, the primary aim of this study is to evaluate the effectiveness of a multifaceted implementation strategy of the PA.

**Methods:**

In a cluster randomised controlled trial (RCT) a multifaceted implementation of the PA will be compared with a minimal implementation strategy of the PA. Participating organisations are a university medical centre, a university and a steel factory. Randomisation will take place at department level. Intervention departments will receive a multifaceted implementation strategy of the PA, which incorporates a working group, supervisor training, and supervisor coaching. Control departments will receive the minimal implementation strategy of the PA, consisting of written information only. The primary outcome measure is self-efficacy of supervisors in joint problem solving to improve work functioning of employees with health complaints and to prevent sick leave. A secondary outcome measure at supervisor level is self-efficacy in communicating with employees about situations of reduced work functioning or being at risk for sick leave. Secondary outcome measures at employee level are attitude, self-efficacy, and social influence, with regard to addressing situations of reduced work functioning or being at risk for sick leave, as well as work functioning, psychological well being, and sick leave. Measurements will take place at baseline, and after six and twelve months follow-up. A process evaluation will be performed as well.

**Discussion:**

This study will be relevant for all organisations with employees at risk for sick leave in health care, education, and industry. Study results will give an insight into the effectiveness of the multifaceted implementation strategy of the PA for supervisors to improve work functioning of employees with health complaints, and to prevent sick leave.

**Trial registration:**

NTR3733

## Background

Sick leave is still a major burden for societies in the Netherlands and other western industrialised countries [1-4]. Besides personal suffering, sick leave also entails extra efforts and costs for organisations and their employees. Human resources (HR) or occupational health services have to take care of sick-listed employees; work remains to be done; colleagues have to take over work; and supervisors may have to support their sick-listed employees. In the Netherlands, the average absence rate was 4.2 percent in 2011, which means a loss of 9 working days per employee per year [3,5]. In addition, direct costs of sick leave for Dutch society in 2010 are estimated at more than €12 billion [2]. By comparison, sick leave costs in the UK in 2013 are estimated at ₤29 billion and in Australia in 2010 at A$30 billion [1,3,4]. This burden of sick leave underlines the urgent need to prevent sick leave.

An effective workplace intervention for organisations to shorten sick leave episodes is the Participatory Approach (PA) [6-9]. PA is a stepwise workplace intervention protocol for supervisors and employees to identify and jointly solve barriers for return to work (RTW). A study by Lambeek et al. demonstrated that an intervention programme with PA for employees sick-listed due to low back pain resulted in a decrease of 120 days to sustainable RTW [8]. Another study also reported that PA is effective for sustainable RTW for employees sick-listed due to distress, if they had the intention to return to work despite symptoms [9]. Although PA is proven to be an effective intervention, it is still not common practice in Dutch organisations [10]. Therefore, an effective strategy for the implementation of PA within organisations may need more research.

Besides applying PA to shorten sick leave episodes, we hypothesize that PA can be used for the prevention of sick leave as well. Although in previous studies PA is applied by an occupational health professional (OHP), for the prevention of sick leave we argue that supervisors, with adequate training and coaching by an OHP, are also able to apply PA. Moreover, supervisors are the first people who can identify employees with reduced work functioning or who are at risk for sick leave due to health complaints. Several studies have already demonstrated the influence of supervisors’ behaviour on work functioning and well-being of employees [11-15]. Hence, we hypothesize that PA applied by supervisors will be effective in improving the work functioning of employees with health complaints and in preventing sick leave.

Regarding the implementation of the PA within an organisation, with reference to the prevention of sick leave, different barriers at organisational, supervisor, employee, and OHP levels exist [10,16,17]. First, the PA does not always correspond well with sick leave policies of organisations. For example, HR may not facilitate modified work for employees with work functioning problems [10,16]. Second, supervisors may experience a lack of self-efficacy in addressing work functioning problems of employees and in jointly realising solutions to these problems [10,16]. Third, supervisors may assume that employees at risk for sick leave – in particular, due to mental health problems – only need rest to recover for functioning at work [10]. Fourth, employees may experience a lack of support, empathy, or the possibility of joint problem solving with their supervisors. They may also encounter insufficient support from HR and organisational policies to recognise and solve work functioning problems [10]. Last, OHPs indicate insufficient knowledge and communication skills of supervisors regarding support for employees at risk for sick leave, or supervisors’ insufficient knowledge as to when to consult an OHP [10,16].

Because of these barriers at different levels, implementation of the PA requires a multifaceted strategy. Shaw et al. showed that working groups combined with training and coaching of supervisors is effective in the prevention of sick leave [17]. This study showed an increase of supervisors’ self-efficacy in their communication with employees with health complaints, a 47% decrease of sick leave episodes, and an 18% decrease of sick leave duration. In general, previous research on implementation of interventions within organisations showed that a multifaceted strategy has proved to be more effective than a single strategy [18]. Moreover, to realise changes within organisations, comprehensive strategies targeted at all different organisational levels are needed [18].

Consequently, the implementation strategy of this study incorporates three components: (1) a working group with representatives of managers, supervisors, employees, HR professionals, and OHPs, (2) supervisor training in PA by in-company OHPs, and (3) coaching of supervisors in PA by in-company OHPs. The main objective of this study is to evaluate the effectiveness of the multifaceted implementation strategy of the PA to increase supervisors’ self-efficacy in joint problem solving for the improvement of work functioning of employees with health complaints, and for the prevention of sick leave. Secondary objectives are: (1) to evaluate the effectiveness of this strategy to improve experienced support and work functioning of employees, (2) to prevent sick leave, and (3) to asses facilitators and barriers for the multifaceted implementation strategy of the PA at all organisational levels.

## Methods

To describe the methods of this study, the CONSORT statement was used [19].

### Study context

In the Netherlands, supervisors are expected to play an important role in the coordination of sick leave of employees and consequently in the prevention of sick leave. The Dutch Gatekeeper Improvement Act directs that employer and employee are both responsible for return to work (RTW). An employer is obliged to start RTW as soon as possible, for example, by offering (other) suitable work, and an employee is obliged to play an active role in the RTW process, for example, accepting other work activities. For this reason most Dutch organisations assign their supervisors as the first point of contact for employees in cases of reduced work functioning or sick leave. After more than six weeks of sick leave supervisor and employee jointly have to draw up a plan of action for RTW. The supervisor also has to manage an RTW file in which all actions and agreements regarding disability and RTW are recorded.

### Study design

This study is a cluster-randomised controlled trial (RCT) in which two implementation strategies will be compared. The PA will be implemented within three organisations: a steel factory, a university medical centre, and a university. Departments of these organisations will be allocated to either the intervention or control group. Intervention departments will receive the multifaceted strategy of the PA and control departments the minimal implementation strategy of the PA. Measurements will take place at baseline and after six and twelve months follow-up. The study protocol has been approved by the Medical Ethics Committee of the VU University Medical Center, Amsterdam, the Netherlands.

### Study population

Supervisors and their employees will be recruited from all three aforementioned organisations. These organisations have about 20,000 employees of which 1,400 have a supervisory role for 10 employees or more. Only departments with participating supervisors will be included in this study. Participation of both supervisors and their employees is voluntary.

#### Inclusion criteria

Eligible supervisors have a minimum age of 18 years, work at least 24 hours per week, and supervise at least 10 employees. Eligible employees have a minimum age of 18 years and work at least 24 hours per week.

#### Exclusion criteria

Supervisors and employees whose contracts will end within one year from baseline or who are not able to fill out questionnaires in the Dutch language will be excluded.

### Randomisation, stratification and blinding

Randomisation will be performed at department level to limit contamination between supervisors of the intervention and control groups. Departments within organisations will be matched as pairs, based on the number of participating supervisors and sick leave frequencies of departments. Randomisation of departments of each pair will be performed by an independent researcher. Inherent in the multifaceted implementation strategy of the PA, it is impossible to blind researchers, supervisors, managers, HR professionals, and OHPs.

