#### Second component: supervisor training

Supervisors will be trained in applying PA by in-company OHPs in a four-hour session and an optional follow-up meeting of two hours. Before supervisor training, in-company OHPs are trained by the research team ([name], [name], [name], [name]) and provided with a training manual. For this study, application of PA is adjusted for the prevention of sick leave and worded in a workplace intervention protocol for supervisors. This protocol consists of seven steps to identify and solve employees’ work functioning problems due to health complaints (see Table 1). The protocol incorporates three supervisor-employee meetings with the supervisor both as participant and process leader. In the first meeting the employee is informed by the supervisor about the protocol and about both their roles in the next meetings. If needed, an employee may ask for an in-company OHP to act as a neutral process leader when applying this protocol.

**Table 1 T1:** Workplace intervention protocol for supervisors

**Meeting 1**	Step 1. Supervisor addresses employee’s reduced work functioning due to health complaints or being at risk for sick leave. Supervisor informs employee about the workplace intervention protocol of the study.
**Preparation**	Step 2. Employee makes an inventory of work tasks and activities, and prioritises work functioning problems within activities. Employee thinks of possible solutions for the two most important work functioning problems.
	Step 3. Supervisor makes an inventory of work tasks and activities for the employee, and prioritises work functioning problems within activities. Supervisor thinks of possible solutions for the two most important work functioning problems.
**Meeting 2**	Step 4. Supervisor and employee discuss work functioning problems and associated solutions, and assess the applicability of these solutions.
	Step 5. Supervisor and employee agree on action plan to realise solutions. If they don’t agree, supervisor asks in-company occupational health professional to act as process leader.
**Realisation**	Step 6. Solutions are prepared and realised.
**Meeting 3**	Step 7. Supervisor and employee evaluate action plan and realised solutions.

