### Statistical analyses

Outcome measures will be compared between both groups at baseline, six, and twelve months follow-up. Primary analyses will be performed at supervisor level and secondary analyses at supervisor and employee level. To assess the success of randomisation, descriptive statistics will be used comparing the baseline measurements of the two groups. In case of unsuccessful randomisation, there will be adjustments for baseline differences. The primary independent variable in the analyses will be binominal representing the allocation to either the intervention or control group. The primary dependent variable is self-efficacy of supervisors in joint problem solving to improve work functioning of employees with health complaints. Changes in primary and secondary outcome variables between baseline and follow-up measurements will be compared between the two groups using linear mixed models at supervisor and employee level. All statistical analyses will be performed according to the intention-to-treat principle and, in case of compliance differences of supervisors, per protocol analyses will be performed as well.

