There are also some limitations. First, recruitment bias may influence results at both supervisor and employee level. Because participation of the supervisor is voluntary, participating supervisors may already be more supportive or interested in supporting employees at risk for sick leave, which could lead to ceiling effects. Supervisors who are not motivated to support employees at risk for sick leave may also be less skilled in supporting. Accordingly, employees who have a bad working relationship with their supervisor or do not want to discuss reduced work functioning due to health complaints will probably be underrepresented. Second, inherent in the multifaceted implementation strategy, it will be impossible to blind researchers, in-company professionals, managers and supervisors for the allocated implementation strategy. In addition, because working groups will take place at organisational level, it is possible that control departments have some benefit from working group results.

Third, data of most outcome measures of this study is self-reported and may be influenced by information or recall bias. For example, it is reasonable that supervisors of the intervention departments will fill out questionnaires at follow-up more accurately than those of the control group. Training and coaching of supervisors will probably create more awareness for questionnaire topics and items. In addition, supervisors in the control group will perhaps be less motivated to fill out questionnaires at follow-up after being allocated to the control group.

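### The protocol rules out blinding for all researchers, but its stated reason does not cover whoever scores and analyses the data, so an available safeguard is given up

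*Protocol article*

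**What the plan says.** The Methods section on randomisation, stratification and blinding states that "it is impossible to blind researchers, supervisors, managers, HR professionals, and OHPs", as something inherent in the multifaceted strategy. The limitations under Methodological considerations repeat it: "it will be impossible to blind researchers, in-company professionals, managers and supervisors for the allocated implementation strategy". Neither place makes an exception for data handling or analysis.

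Four other statements bear on the point:

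- **Allocation.** "Randomisation of departments of each pair will be performed by an independent researcher" (same Methods section).
- **Who trains whom.** "Supervisors will be trained in applying PA by in-company OHPs in a four-hour session", and "Before supervisor training, in-company OHPs are trained by the research team" (Second component: supervisor training).
- **Baseline adjustment.** "In case of unsuccessful randomisation, there will be adjustments for baseline differences" (Statistical analyses). Success of randomisation is to be assessed by describing baseline measurements in the two groups.
- **Analysis sets.** Every analysis follows intention-to-treat. A second set is added only on a condition: "in case of compliance differences of supervisors, per protocol analyses will be performed as well" (Statistical analyses).

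The primary outcome is a three-item, seven-point self-efficacy score completed by the supervisors (Primary outcome measure). Data come from online or paper questionnaires (Data collection procedure). Sick leave also comes from databases of HR and the contracted occupational health services (Sick leave).

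**The concern.** The reason given for not blinding is a property of the intervention: people who run or attend working groups, training and coaching know that they do so. Scoring a questionnaire and fitting a mixed model require no such knowledge. The statement therefore reaches further than its reason.

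Most other stages of this trial cannot be masked. The supervisors who rate themselves know their arm, and the research team prepares the OHPs who deliver the training, so it is involved in the strategy that it evaluates. Analysis is one of the few stages where masking is still possible. One choice there affects the primary model, namely whether to adjust for baseline differences, and it turns on a comparison of the arms once baseline data exist. An analyst who knows which arm is which could let that choice, or choices in scoring and cleaning, lean towards the intervention.

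**Working it through.** No printed figure of the plan is in dispute, so the main check is of the text. The arithmetic only sizes the adjustment choice.

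**1. Does the stated reason cover each group?**

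| Group | Why it would know the allocation | Covered by the reason? |
|---|---|---|
| Supervisors | Receive training and coaching | Yes |
| OHPs | Deliver training and coaching | Yes |
| Managers, HR professionals | Belong to the organisation; represented in working groups | Yes |
| Researchers who train OHPs | Prepare the delivery | Yes |
| Whoever scores and analyses the data | Only if the file shows it | No |

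Allocation enters the models as one two-level variable (Statistical analyses), which can carry neutral codes. A researcher independent of the team already performs the randomisation and so could hold the key.

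**2. Which conditional steps can alter the primary test?** Baseline adjustment can, because it changes the primary model. The per-protocol analysis cannot, because it is added to intention-to-treat and does not replace it.

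**3. How much could a free choice of adjustment matter?** Assume two test statistics, adjusted and unadjusted, standard bivariate normal under the null with correlation r, each tested two-sided at 0.05. If the better one is reported, the false-positive risk is

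P = 1 − Pr(|Z1| ≤ 1.96 and |Z2| ≤ 1.96).

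| Assumed r | P |
|---|---|
| 0.9 | 7.0% |
| 0.8 | 7.8% |
| 0.7 | 8.3% |

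The article gives no value for r. As a cross-check, take the two candidates to be a change-score test and a test adjusted for the baseline score. Assume 43 supervisors per arm (107 × 0.80 / 2 = 42.8), no clustering, and a baseline-to-follow-up correlation ρ of 0.3, 0.5 or 0.7. Simulation with 20,000 trials each gives 7.7%, 7.6% and 6.6% for the smaller p-value, against about 5% for either test fixed in advance. For these two tests r = √((1 + ρ)/2), which is 0.81, 0.87 and 0.92, so the two calculations agree.

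**4. Does coding the arms lower these figures?** No. Exchanging labels A and B turns z into −z and leaves |z| unchanged. A masked analyst sees the same two p-values. Only an adjustment fixed before follow-up outcomes are analysed brings the risk back to 5%. Masking does something different: it stops choices being steered in a known direction.

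**The case against.** The strongest reply is that this turns on one broad word in a condensed article. Read in context, it may mean the team that trains OHPs and runs the study, which does know the allocation, and the article discloses the lack of blinding as a limitation. Who analyses the data, the criterion for imbalance and the per-protocol definition may all be in an analysis plan that is not shown. That stands for those details, and none of them is counted here as missing. It does not rescue the blinding statement, which is a positive claim made twice without exception. An analysis plan that masked the analyst would contradict it.

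It is also fair that the benefit is limited. Masking the analyst does nothing about self-report by unblinded supervisors, and the codes may be partly guessable from the data.

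A reader might infer more than the text supports:

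- **That the researchers deliver the supervisor training.** They do not. In-company OHPs deliver it, and the research team trains the OHPs.
- **That unblinded researchers are given two decisions that depend on results.** The triggers are baseline and compliance differences, not outcome results, and the article assigns the decisions to no one.
- **That the false-positive risk is 7.0% to 8.3%.** Nothing says that anyone will pick the better of two tests.

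**Conclusion.** The point holds in limited form. The article declares blinding of researchers impossible for a reason that does not apply to those who score and analyse the data, and so wrongly excludes a usable safeguard. This matters because the primary outcome is an unmasked self-report and the form of the primary model depends on a comparison of the arms.

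The size is modest. The 7.0% to 8.3% range is a worst case that rests on assumed correlations and on selective reporting, and it belongs to the open adjustment rule rather than to the lack of coding. The conclusion about the wording does not depend on it. This is a cheap improvement, not a flaw that invalidates the design.

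**What to change.** 1. In both places, limit the statement to supervisors, managers, HR professionals, OHPs and the researchers who train OHPs.
2. Do scale scoring and the primary analysis on a file in which the independent researcher who randomised the departments has coded the arms A and B and replaced department names with codes. Keep cluster and pair identifiers so that the models can still use them. Extraction of sick leave from HR and occupational health databases comes before such a file exists and stays outside the masking.
3. Before any follow-up outcome is analysed, fix the baseline adjustment of the primary model and write down what counts as per-protocol compliance. Only the definition can be set then; whether compliance differed has to wait for the data.
4. Merge compliance data that reveal the arm only after the primary model has been run.

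The cost is a change of wording, some file preparation, a short delay before compliance data are merged, and an added task for the independent researcher, whose only stated role is randomisation. Sample size, alpha and power do not change.
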